Here, were report the plans for and design of a study that will evaluate the effects of YKSCH on sleep improvement in patients with PD experiencing sleep disturbance. This study will be a prospective, randomized, double-blinded, placebo-controlled, parallel-group pilot trial. The subjects will be patients with PD who are experiencing sleep disturbances, and these subjects will be randomly assigned to a treatment group or control group at a 1:1 ratio. The intervention will be YKSCH administration in the treatment group and placebo administration in the control group. Subjective and objective assessments of sleep improvement will be performed in this study using a questionnaire survey instrument, polysomnography (PSG), and sleep-related hormone measurements. To elucidate the mechanism underlying the effects of YKSCH in PD, hemodynamic changes in the frontal lobe will be measured using functional near-infrared spectroscopy (fNIRS), and the levels of neurotransmitters (NTs) related to PD will also be evaluated.

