### Study design and setting

2.1

This study will be a randomized, placebo-controlled trial to identify the efficacy of YKSCH in the treatment of sleep disturbance in PD. During the clinical trial period, all the subjects will be allowed to undergo any combination therapy, such as conventional medicine treatment, non-pharmacotherapy, and exercise therapy, except herbal medicine treatment. In combination therapy, the dosage of anti-PD conventional medication will have to have been stable for at least 1 month prior to enrollment. The primary outcome measure will be the Scales for Outcomes in PD-Sleep Scale (SCOPA-S) score, and the secondary outcome measures will be PSG findings; results of questionnaire survey on non-motor symptoms in PD; changes in NTs and hormone levels, hemodynamic changes in the PFC, as measured by fNIRS in patients with PD. Descriptions of selection of subjects, clinical outcomes, and safety assessment are presented in Table 1. The study setting and site of data collection is the Clinical Trial Center at Dunsan Korean Medical Hospital of Daejeon University in South Korea.

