#### Secondary outcomes

2.6.2

The secondary outcome measures include findings from 5 instruments evaluating sleep disorders, PSG and sleep-related hormone analysis, changes in the levels of NTs associated with PD, and hemodynamic changes in the PFC during verbal fluency task of subjects.

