#### Molecular analysis: plasma and serum levels of neurotransmitters

2.6.5

Investigation of changes in the plasma and serum NT levels may help us to understand the mechanism of action of YKSCH in patients with PD experiencing sleep disturbance. The serum levels of the PD-related NTs, dopamine, GABA, glutamate, norepinephrine, epinephrine, and serotonin, will be analyzed.^[28]^ Blood collected from the patients in both groups, at baseline (visit 1) and after treatment (visit 4), will be immediately centrifuged at a temperature below 4°C. The obtained plasma and serum samples will be stored at a temperature below −80°C until further analysis. The samples will be analyzed by Seoul Clinical Laboratories in South Korea, a quality facility certified by the European Quality Assurance Agency. The levels of dopamine, epinephrine, and norepinephrine will be measured using a high-performance liquid chromatography-electrochemical detection system (Agilent Technologies, Santa Clara, CA). The glutamate and GABA levels will be measured using ion-exchange chromatography (Biochrom Ltd., Cambourne, Cambridge, UK). The serotonin levels will be measured using the ELISA Fast Track kit (Labor Diagnostika Nord, Nordhorn, Germany). For hormone analysis, the subjects will be asked to abstain from drinking, smoking, and consumption of caffeine, turkey meat, bananas, and tomatoes, beginning the day before the test, as these can affect sleep rhythm and melatonin secretion.^[8]^ The night before hormone analysis, the subjects will be instructed to turn off the lights and attempt to sleep at 10 pm, and the use of electronic devices, such as smart phones and televisions, will be prohibited on the day before the evaluation.

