#### Sample size

2.9.1

Designed to study the effects of YKSCH in patients with PD experiencing sleep disturbance, this pilot study will use the SCOPA-S score as the primary outcome. A total of 34 subjects (17 in each group) will be needed, based on the effect size demonstrated in a previous study on the effect of doxepin against insomnia in patients with PD,^[9]^ allowing a dropout rate of 10%, a two-sided significance level of 5%, and 80% statistical power.

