#### Statistical analysis

2.9.2

Statistical and fNIRS data analyses will be performed by statisticians and a researcher from a different group. An intention-to-treat analysis will be performed in case of subjects lost to follow-up, and multiple imputations will be applied for the missing data. Statistical analysis will be performed using SPSS software for Windows, version 24.0, (Chicago, IL). The SCOPA-S score, which is the primary outcome, will be evaluated by calculating the difference between the mean scores before and after receiving YKSCH or placebo (for treatment or control groups, respectively). Independent two-sample *t*-test (or the Mann–Whitney *U* test for nonparametric samples) will then be performed to analyze the difference between the treatment and control groups. The results of the questionnaire survey, including PDSS, ESS, NPI, BDI, and PSS, scored at 0, 4, 8, and 12 weeks, respectively, and NT levels measured at 0 and 12 weeks will be analyzed using independent two-sample t-tests (or the Mann–Whitney *U* test for non-parametric samples). To compare sleep metrics obtained using PSG and measurement of hormone levels, pre- and post-YKSCH or placebo treatment at weeks 0 and 12, paired t-tests (or the Wilcoxon signed-rank test) will be used. The mean oxyhemoglobin and deoxyhemoglobin concentrations determined using fNIRS at 0 and 12 weeks will be analyzed using repeated-measures analysis of variance. Pearson's correlation coefficient will be used to assess the association among subscales of the questionnaire surveys, oxyhemoglobin and deoxyhemoglobin concentrations, and NT levels. The level of statistical significance will be set at *P < *.05, and 95% confidence intervals will be calculated. A statistician will be consulted incase the obtained data need to be calibrated.

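### Neurotransmitters are defined as a change from baseline, but the written test compares levels and names no use of the baseline sample

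*Protocol article*

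**What the plan says.** Three places in the protocol article describe the NT outcome as a change. Section 2.1 (Study design and setting) lists "changes in NTs and hormone levels" among the secondary outcomes. Section 2.6.2 (Secondary outcomes) has "changes in the levels of NTs associated with PD". Section 2.6.5 (Molecular analysis) gives the purpose: "Investigation of changes in the plasma and serum NT levels may help us to understand the mechanism of action of YKSCH". Section 2.6.5 also has blood taken from both groups at visit 1 and visit 4, so a baseline value is planned for every subject.

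Section 2.9.2 (Statistical analysis) then states that "NT levels measured at 0 and 12 weeks will be analyzed using independent two-sample t-tests", or by the Mann–Whitney U test. The same sentence covers PDSS, ESS, NPI, BDI and PSS at weeks 0, 4, 8 and 12.

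The other outcomes in that paragraph each get a method that uses both time points. SCOPA-S has a before-after difference that is then compared between arms, PSG and hormones have paired tests, and fNIRS has repeated-measures analysis of variance.

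**The concern.** The outcome is a change, but the quantity named for testing is a level. Taken as written, the sentence yields two between-arm tests per NT.

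- **Week 0.** This compares two randomised groups before any treatment. It cannot inform the question of whether YKSCH alters NT levels.
- **Week 12.** This carries the treatment information, but stable differences between subjects stay in the error term although a baseline measurement exists that could remove part of them.

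NTs are one of the two measures the article puts forward for the mechanism of action, the other being fNIRS. With 17 subjects per arm there is little precision to spare. If r is moderate or high, a real NT effect is more likely to be missed than it need be.

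**Working it through.** **The plan's own figure.** Section 2.9.1 states: "A total of 34 subjects (17 in each group) will be needed". It borrows its effect size from an earlier doxepin trial and assumes 10% dropout, a two-sided 5% level and 80% power. The effect size is not printed, so 34 cannot be reproduced forward. Working backward, 17 × 0.9 = 15.3, or about 15 evaluable per arm. At two-sided 5%, 80% power with 15 per arm needs a standardised difference of about 1.06 (noncentral t). That calculation concerns SCOPA-S only; no power is stated for NTs.

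**Inputs for the NT check.**
- From the article: 1:1 allocation, 17 per arm (about 15 after 10% dropout), two-sided 5%.
- Assumed, because the article gives no such figures: an effect of 0.5 between-subject SD, equal SD at both visits, and r from 0.3 to 0.8.

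**Formulas.** With n per arm, the noncentrality parameters are:
- week-12 level only: λ = 0.5 × √(n/2), df = 2n − 2
- change score: λ / √(2(1 − r)), df = 2n − 2
- ANCOVA on baseline: λ / √(1 − r²), df = 2n − 3

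**Numbers in.** For n = 17, λ = 0.5 × √8.5 = 1.458. For ANCOVA this becomes:
- r = 0.5: 1.458 / 0.866 = 1.68
- r = 0.7: 1.458 / 0.714 = 2.04
- r = 0.8: 1.458 / 0.6 = 2.43

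For n = 15, λ = 0.5 × √7.5 = 1.369.

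**Power.**

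| r | n per arm | week 12 only | change score | ANCOVA |
|---|---|---|---|---|
| 0.3 | 17 | 0.29 | 0.22 | 0.32 |
| 0.5 | 17 | 0.29 | 0.29 | 0.37 |
| 0.7 | 17 | 0.29 | 0.45 | 0.51 |
| 0.8 | 17 | 0.29 | 0.61 | 0.65 |
| 0.3 | 15 | 0.26 | 0.20 | 0.28 |
| 0.5 | 15 | 0.26 | 0.26 | 0.33 |
| 0.7 | 15 | 0.26 | 0.40 | 0.46 |
| 0.8 | 15 | 0.26 | 0.55 | 0.60 |

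The ANCOVA formula ignores the small cost of chance baseline imbalance. A simulation with 17 per arm gave 0.36, 0.49 and 0.64 at r = 0.5, 0.7 and 0.8, within about 0.02 of the formula.

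**Reading the table.** At r = 0.7, adjustment is worth 1 / (1 − 0.49) = 1.96 times the sample size. As a share of the ANCOVA power with 17 per arm, the week-12 test gives up:
- r = 0.5: (0.37 − 0.29) / 0.37 = 22%
- r = 0.7: (0.51 − 0.29) / 0.51 = 43%
- r = 0.8: (0.65 − 0.29) / 0.65 = 55%

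If the effect is instead set so that ANCOVA has 80% power, the week-12 test falls below 40% only when r exceeds about 0.79.

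**The case against.** The strongest reply is that the sentence is compressed. The text just before it forms a before-after difference for SCOPA-S and applies the same two-sample test, and the outcome sections speak of change. The authors may therefore mean a t-test on the week 0 to 12 change, with the detail left to a fuller document. That reading is possible, but it is not what is written, and the paragraph is explicit about the difference for SCOPA-S. Nor would it remove the reason to revise: in the table ANCOVA beats the change score at every r shown, and a plain change score does worse than the week-12 test below r = 0.5.

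A reader might also infer stronger faults that the document does not support:

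- **That most of the power is lost.** This needs r of about 0.8 or more, and no correlation is given.
- **That a chance week-0 difference would produce a false YKSCH effect.** Such imbalance is part of the sampling variation that the week-12 test already allows for. Under randomisation its error rate stays at 5% and its estimate is unbiased.
- **That skewed levels would cripple the planned test.** The same sentence offers Mann–Whitney, which in simulation on these assumptions had power of about 0.27, close to the t-test on log levels.

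It is also fair to say that NTs are secondary, that the trial calls itself a small pilot, and that it was sized on SCOPA-S alone. Up to r = 0.8, even ANCOVA reaches no more than 0.65 under these assumptions, so no NT result here would be decisive. That limits the weight of the point without answering it.

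**Conclusion.** The mismatch stands on the text: a change outcome is paired with a test of levels that names no use of baseline. The consequence is lost precision, not bias or an inflated error rate. For an assumed 0.5 SD effect and 17 per arm, the shortfall against ANCOVA is 8, 22 and 36 percentage points of power at r = 0.5, 0.7 and 0.8; at r = 0.3 it is about 3 points. With 15 per arm it is 7, 20 and 34 points at r = 0.5, 0.7 and 0.8. The effect size, the equal SDs and r are all assumptions, so the direction is firm and the size is not. The point is worth correcting because the remedy is free, but it concerns secondary outcomes in a pilot.

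**What to change.** Rewrite the NT part of section 2.9.2. For each of the six NTs, make one between-arm comparison of the week-12 level with the week-0 level as covariate (ANCOVA), and report the adjusted difference with its 95% confidence interval. If the levels prove skewed, log-transform both values, in which case the result reads as a ratio. Drop the between-arm test at week 0 and show baseline levels descriptively by arm.

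Apply the same baseline adjustment to PDSS, ESS, NPI, BDI and PSS at their post-baseline visits, since the same sentence governs them.

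The cost is a sentence or two in the analysis section and one degree of freedom per model. It needs no new visits, samples or assays.

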### Randomization and blinding

2.4

The allocation to placebo control or YKSCH treatment group of subjects meeting the eligibility criteria will be performed by an independent statistician via computer-generated block randomization. For assessing secondary outcomes, PSG and hormone analysis will be performed for some of the subjects from the treatment and control groups at a 1:1 ratio; the subjects will be selected by an independent statistician, using systematic sampling. Each subject will receive an identification code enclosed in an opaque envelope. The identification code shall indicate whether PSG and hormone analysis will be performed. The subjects, researchers, and assessors collecting the data will be blind to group assignment, as this study is designed to be double blind. If unblinding is required, such as occurrence of medical emergency, the principal investigator decides to remove the blindness through the researchers’ meeting. In this case, the institutional review board (IRB) should be informed of the unblinding and explain the medical emergency in detail within 24 hours enrollment of subjects, allocation sequence, and assignment of subjects will be the responsibility of the Clinical Trial Center at Dunsan Korean Medical Hospital of Daejeon University.

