#### Polysomnography and hormone analysis

2.6.4

For objective sleep assessment, total recording time, sleep period, waking after sleep onset, total sleep time, sleep onset, sleep efficiency, number of awakenings, sleep latency to N1, sleep latency to N2, sleep latency to N3 (slow wave sleep), and stage R latency from sleep onset will be measured using PSG (Embletta MPR PG, Natus Medical Incorporated, Pleasanton, CA, USA). The subjects will be examined using in-laboratory PSG for one night. The PSG assessment will be set up and performed by a trained sleep technologist, using an Embletta MPR.^[26]^ This device consists of multiple channels for electroencephalography, electrocardiography, electrooculography, airflow, etc. Recordings from the electroencephalogram channels (C3-M2, C4-M1, O1-M2, O2-M1, F3-M2, and F4-M2) in the frontal, central, and occipital regions of the head, electrooculography channels (LOC-M2 and ROC-M1), and electromyography channel (EMG1-EMG2) in both legs will be acquired for each subject. Nasal and oral airflow, recorded using oral/nasal thermistor airflow and pressure nasal cannula, will be measured. In addition, oxygen saturation, using pulse oximetry; movements of the chest and abdomen; behavior during sleep, using video recording; change of body position, such as supine, left, right, prone, and upright, and snoring; and pulse rate will be recorded. Scoring of the sleep stages will be performed according to the American Academy of Sleep Medicine rules.^[27]^ Blood sampling, for measurement of cortisol and melatonin levels, will be conducted every 4 hours, over 24 hours, via venous catheter. Hormone levels will be examined using a melatonin enzyme-linked immunosorbent assay (ELISA) kit (ab213978; Abcam, Cambridge, MA) and a cortisol parameter assay kit (KGE008B, R&D systems, Minneapolis, MN).

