## Discussion

3

Sleep disturbance is one of the most clinically significant non-motor symptoms of PD, and encompasses many symptoms such as insomnia, daytime sleepiness, restless legs syndrome, and rapid eye movement sleep behavior disorder, causing many inconveniences and stress to patients and caregivers.^[9,33]^ The characteristics of sleep disorder in PD are multifactorial and multidimensional, with overlapping symptoms.^[4]^ Therefore, assessing sleep disturbance in PD using a single instrument is difficult. To conduct a subjective as well as objective assessment of sleep disturbance, questionnaires on sleep, PSG, and hormone (cortisol and melatonin) analysis will be employed in concert in this study.

Subjective instruments to assess sleep disturbance, such as SCOPA-S, PDSS, and ESS, will be used as outcome measures in this study. The SCOPA-S and PDSS are used for specific assessments of sleep disturbance in PD.^[22]^ The SCOPA-S measures both nocturnal disturbance and day-time sleepiness. The PDSS measures nocturnal disability, and helps to identify the potential causes of sleep disorder.^[21,23]^ It has been validated to reflect observations of the patients and caregivers,^[34]^ and its clinical usefulness has been demonstrated.^[35]^ The ESS is used to measure day-time sleepiness.^[23]^ In addition, NPI, BDI, and PSS, questionnaire surveys on neuropsychiatric problems and stresses correlated with sleep disorder, have been selected for assessment of secondary outcomes.

In a previous study using PSG for an objective assessment, increased sleep latency, reduced sleep efficiency, and reduced rapid eye movement sleep in patients with PD have been reported.^[7]^ In a previous study on the use of microsubthalamotomy to improve sleep disturbance in patients with PD, the PSG data evidenced increased total sleep time and sleep efficiency, and decreased wakefulness after sleep onset and arousal index.^[10]^ In previous studies on circadian rhythms, amplitude of the melatonin rhythm was significantly lower during excessive day-time sleepiness in PD,^[36]^ and serum cortisol and circulating melatonin levels in early PD were elevated and reduced, respectively.^[7]^ Therefore, this study will seek to investigate, through PSG, whether YKSCH improves sleep time and efficiency, while further investigating the effects of cortisol and melatonin on sleep rhythm.

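### PSG and hormone outcomes are assigned only within-arm before/after tests, which cannot show whether YKSCH rather than placebo improved sleep

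*Protocol article*

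**What the plan says.** The Introduction describes a "randomized, double-blinded, placebo-controlled, parallel-group pilot trial". Section 2.4 (Randomization and blinding) states that "PSG and hormone analysis will be performed for some of the subjects from the treatment and control groups at a 1:1 ratio", so placebo data on these outcomes will exist. Section 2.6.4 adds that "The subjects will be examined using in-laboratory PSG for one night".

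Section 2.9.2 (Statistical analysis) then names a test for each family of outcomes:

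- SCOPA-S: a two-sample t-test or Mann–Whitney test on the before/after difference, which "will then be performed to analyze the difference between the treatment and control groups".
- The five questionnaires and the neurotransmitters: also between-arm. For example, "NT levels measured at 0 and 12 weeks will be analyzed using independent two-sample t-tests".
- PSG metrics and hormone levels: "pre- and post-YKSCH or placebo treatment at weeks 0 and 12, paired t-tests (or the Wilcoxon signed-rank test) will be used".

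No other sentence in the article gives PSG or hormones a between-arm test, and the planned correlation analysis does not include them. Yet the Discussion says that "this study will seek to investigate, through PSG, whether YKSCH improves sleep time and efficiency".

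**The concern.** The question put to PSG is causal: does YKSCH improve sleep? The named test compares each subject with his or her own baseline, one arm at a time. A change from week 0 to week 12 in the YKSCH arm mixes any drug effect with everything else that moves over 12 weeks:

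- placebo response;
- regression to the mean, which is plausible because entry requires a raised SCOPA night score (section 2.3.1);
- adaptation to a second single-night laboratory recording.

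The concurrent placebo arm exists to remove these, and a within-arm test does not use it.

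PSG and hormones are what the Discussion relies on for the objective assessment of sleep. If they are analysed only as written, an improvement in the YKSCH arm could not be attributed to YKSCH.

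**Working it through.** **1. Is there a figure of the plan's own to reproduce?** Not for these outcomes. The only power statement, in section 2.9.1, concerns SCOPA-S: 34 subjects, "allowing a dropout rate of 10%, a two-sided significance level of 5%, and 80% statistical power". It prints no effect size, so it can be neither confirmed nor refuted. Worked backwards, 15 evaluable per arm (15/0.9 = 16.7, rounded up to 17) corresponds to a standardised difference of about 1.06 by the noncentral t distribution. This has no bearing on the PSG and hormone subset, whose size is not given.

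**2. Can the sentence be read as a between-arm test?** There are two possible readings. If the paired test is run in each arm separately, it yields two within-arm p-values and no estimate of the difference between arms. If both arms are pooled, it estimates the average change over all subjects, which contains no treatment contrast. Neither reading gives a comparison of YKSCH with placebo.

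**3. How often would a within-arm test mislead?**

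Inputs:
- two-sided 5% level (section 2.9.1; section 2.9.2 sets P < .05);
- n = 8 per arm, an assumption (about half of each arm of 17);
- no drug effect, so both arms have the same mean change δ in SD units of the within-person change. δ is an assumption, varied from 0 to 0.7.

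Formulas, for a paired t-test with n − 1 = 7 degrees of freedom, critical value 2.365 and noncentrality δ√n:
- U = P(T > 2.365), a significant improvement in one arm;
- L = P(T < −2.365), a significant worsening;
- the arms are independent, so P(YKSCH significantly improved, placebo not significant) = U × (1 − U − L).

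| δ | δ√8 | U (YKSCH arm taken by itself) | L | U × (1 − U − L) |
|---|---|---|---|---|
| 0 | 0 | 0.025 | 0.025 | 0.025 × 0.950 = 0.024 |
| 0.1 | 0.283 | 0.043 | 0.014 | 0.043 × 0.943 = 0.041 |
| 0.2 | 0.566 | 0.071 | 0.007 | 0.071 × 0.922 = 0.066 |
| 0.3 | 0.849 | 0.111 | 0.003 | 0.111 × 0.886 = 0.098 |
| 0.5 | 1.414 | 0.231 | 0.001 | 0.231 × 0.768 = 0.178 |
| 0.7 | 1.980 | 0.401 | 0.000 | 0.401 × 0.599 = 0.240 |

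A direct two-sided between-arm test at 5% wrongly favours YKSCH with probability 0.025, whatever the shared change.

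**4. Sensitivity to the subset size.** The last column at δ = 0.3 and 0.5 becomes 0.07 and 0.12 with 5 per arm, 0.12 and 0.21 with 10, and 0.15 and 0.25 with 15.

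**The case against.** Much can be said for the plan:

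- These are secondary outcomes, measured in part of a trial that calls itself a small pilot. The SCOPA-S comparison is between arms and is untouched, as are sample size, randomisation and data collection.
- The size of the problem depends on a shared change that the documents do not give. With no shared change, the pattern in the last column of the table is no more frequent than a false positive from a direct test (0.024 against 0.025).
- A statistical analysis plan that is not shown might add a between-arm test.

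The first two points stand and limit the severity. The third does not remove the problem. The article does not leave the test open. It fixes a paired test for these outcomes beside independent-sample tests for the others, so the published text would need correcting in any case.

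A reader might also infer three stronger things that the documents do not support:

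- *That YKSCH will be judged by a significant result in its arm and a non-significant one under placebo.* The plan states no such rule. It is a foreseeable misreading of two within-arm p-values, and the last column of the table applies only if someone makes it.
- *That the error rates are those for 17 per arm.* Section 2.4 restricts PSG and hormones to some of the subjects, so the full arms do not apply.
- *That sampling every 4 hours over 24 hours makes a paired test unsuitable for the hormones, forcing one test per clock time or treating correlated samples as independent.* Reducing each profile to one value per subject and visit is ordinary practice, and an article may leave that derivation to the full protocol or analysis plan.

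**Conclusion.** The point holds. Section 2.9.2 fixes the wrong contrast for PSG and hormones, and as written these outcomes cannot answer the Discussion's question about YKSCH.

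With 8 per arm and no drug effect, the YKSCH arm taken by itself shows a significant improvement with probability 0.11 at a shared change of 0.3 SD and 0.23 at 0.5 SD. If readers took significance under YKSCH but not under placebo as evidence, that would arise in YKSCH's favour with probability about 0.02 with no shift, 0.10 at 0.3 SD, 0.18 at 0.5 SD and 0.24 at 0.7 SD, against 0.025 for a direct test. The subset size and the shared change are assumptions. The conclusion that the contrast is wrong depends on neither.

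It should be fixed, but it does not threaten the trial's main result, because the outcomes are secondary, the trial is a pilot and the primary analysis compares the arms.

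**What to change.** In section 2.9.2, replace the paired tests as the main analysis of PSG and hormone outcomes with a between-arm comparison reported with its 95% confidence interval. ANCOVA of the week 12 value on arm and the baseline value of the same measure is the more efficient choice. The two-sample test of change already planned for SCOPA-S is the minimum and would also cure the defect. For the hormones, apply it to one summary value per subject and visit. Keep the within-arm changes and paired tests as description only. Make the change before unblinding.

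The cost is wording; no new data are needed. The downside is wide intervals. With 8 per arm, the half-width for a difference in mean change is 2.145 × √(2/8) = 1.07 SD of the change (2.145 being the t quantile on 14 degrees of freedom). That is the precision such a subset can give on the treatment difference.
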